**Maintenance Intervention (Months 7 through 12)**		

**Type of contacts**	**Frequency**	

	**Months 7 through 12**	**Months 13 through 18**

**Group weight management class** Overall frequency	Once per month	Once per month

Led by interventionist	Monthly	Monthly

**Individual visit **with interventionist	Every 4 weeks	Every 4 weeks

**Group physical activity class** Overall frequency	Three times per week	Three times per week

Led by exercise leader/interventionist	Twice per week	Once per week

Monitored by rehab program staff	Once per week	Twice per week

**Weigh-in** Overall frequency	Twice per month	Twice per month

With intervention staff	Twice per month	Twice per month

**Core Components**		

Self-monitoring	Weigh-ins, Tracker food/exercise log	

Goal setting, feedback, problem solving	Motivational interviewing and support at group and individual sessions	

Social support	Group and individual weight management sessions, group physical activity sessions	

Skills training	Weight management group sessions, physical activity sessions, individual sessions	

Environmental supports	Physical activity sessions, Staff education in health food choices on-site	

Environmental contingencies/reinforcements	incentive items for attendance, participation and specific behaviors	

Group weight-management classes occur three times per month during the intensive phase of the intervention and each month the classes are focused on one main topic, such as increasing fruit and vegetable consumption. The sessions begin with a discussion to support and review the concepts discussed and practiced since the prior session. A portion of the weekly session is devoted to didactic information about healthy eating or physical activity education, which is supported by food models and posters, a self-monitoring worksheet, hands-on activities related to the monthly topic, or food tastings. Participants set individual behavioral goals based on the material presented that week.

Group physical activity sessions are held three days per week at the rehabilitation center (e.g., in a multipurpose area) and led by a trained exercise leader from the study staff. A progressive exercise program starts at a level appropriate for sedentary adults: 10-minute warm-up; 10 minutes of moderate intensity physical activity and 5-minute cool down [45]. The exercise duration gradually increases each week until participants are completing 40 minutes of moderate intensity physical activity and 10 minutes of warm-up and cool-down. Participants are encouraged to incorporate daily physical activity outside of the group exercise class and may set goals that reflect this effort.

In addition to the organized sessions, participants meet with the intervention staff monthly for an individual weight loss counseling session. This brief activity provides immediate feedback on weight loss progress. If participants lose weight, they are asked what worked for them. If they gain weight, staff work to problem-solve and assist in working towards a behavioral goal or setting a more realistic goal.

Self-monitoring and positive reinforcement are important aspects of successful weight loss trials. Participants are asked to fill out a "Tracker" as a self-monitoring tool outside of group sessions. Each tracker is used for one week; participants record the number of servings of fruits and vegetables, and respond yes or no to: exercising for 30 minutes; drinking sugar drinks; eating junk food; smart portions or smart snacks. The Tracker provides a behavioral cue to participants. An incentive program rewards participation in class and individual sessions with choices of varying priced items (e.g., gym suit, store gift card) after a specified number of stickers have been earned. In order to earn a sticker in exercise class the participant must remain standing and engaged in class from the first minute of warm up through the last minute of cool down. For weight management group and individual visits, participants earn a sticker for being present in class throughout the entire duration of the session time.

For the maintenance intervention period, rehabilitation center staff assumes the responsibility for much of the exercise portion of the intervention in a stepped process over two 6-month phases. Designated rehabilitation center employees are trained by intervention study staff and provided with exercise videos made by the study team in an effort to mimic the instructor led exercise class as much as possible. The rehabilitation staff take responsibility for encouraging attendance and participation, starting the video, overseeing the safety of the class, and recording attendance data. Intervention study staff are available for consultation as needed to offer more support during this phase. This transition occurs in order to facilitate the rehabilitation center's ownership of the program, with the goal of increasing the likelihood that the center will continue to offer components of the intervention after the study is complete.

### Intervention Delivery

ACHIEVE interventionists are skilled facilitators with experience in behavior change and group and individual-level counseling. Interventionists have a skill level that would be typical for a community health educator with a bachelor's degree; exercise leaders have at least one year of experience in leading an exercise class and/or are a certified exercise instructor. Intervention staff are trained to deliver any or all components of the intervention in order to maximize the resources of this multi-site trial. Manualized procedures and standardized materials are used to ensure consistency of the intervention including standardized formats for the group exercise classes. Staff members are regularly observed as part of ongoing staff training and fidelity assurance.

Psychiatric rehabilitation program leadership and staff at each site support the intervention and are involved in the study on multiple levels. Program leadership from each site work with the study team so that intervention classes fit into the overall center schedule, and collaborate on participants' individual rehabilitation plans. Each site designates at least one employee to become trained to conduct group physical activity classes using an exercise video.

Resources included in measuring the costs of the intervention delivery include the number of staff, and the duration of each activity. For each study site, staff record one week of data at intervention months 2, 3, 5, 6, 12, 15 and 18. Staff time includes time with participants for intervention sessions, time spent preparing for sessions, training and intervention-related meetings. All research related activities are excluded from the cost analysis.

### Control Group

Participants in the control group receive standard nutrition and physical activity written information at baseline. Health classes are held quarterly for control participants with content unrelated to weight loss (e.g., cancer screening, oral health).

### Environmental Nutrition Intervention

In order to support intervention group participants' ability to select healthy foods, interventionists provide consulting services to rehabilitation program kitchen staff. The consultation sessions help kitchen staff identify healthier food choices for meals served on-site within site budget and regulatory constraints (e.g., federal food guidelines). Interventionists work with rehabilitation staff to identify goals and then offer options to improve food choices such reducing high sugar foods, working on appropriate portion sizes and modifying vending machine offerings. Rehabilitation staff choose goals and which options they will incorporate.

A random sample of menus at baseline, 6 months, and 18 months are collected and evaluated for nutritional content using ESHA software (The Food Processor, 2009, Salem, OR) [46].

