## Methods

### Study Design Summary

The core design is a randomized, two-arm, parallel, multi-site clinical trial. Inclusion/exclusion criteria were chosen to enroll a population with chronic mental illness who are overweight or obese and who may safely participate in a weight loss intervention including moderate intensity exercise. Interested mental health consumers are being screened for eligibility at 10 psychiatric rehabilitation centers across Maryland. Three hundred and twenty adult participants completing screening are targeted for enrollment and randomization to the ACHIEVE (Achieving Healthy Lifestyles in Psychiatric Rehabilitation) intervention or usual care. Intervention participants receive group and individual weight management sessions and group physical activity classes. In the initial 6-month intervention phase, study interventionists lead the sessions and also train designated rehabilitation program staff. A 12-month maintenance intervention phase follows in which interventionists continue leading some sessions and trained rehabilitation staff assume responsibility for delivering part of the intervention. Interventionists also provide education to rehabilitation program kitchen staff to increase options for healthy meals served on-site. Follow-up data collection occurs at 6, 12, and 18 months from baseline. The study was approved by the Johns Hopkins Institutional Review Board (protocol number NA00015231).

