### Data Collection and Measurements

Before formal screening for the trial begins, oral consent from rehabilitation center attendees is obtained and their weight and height at study baseline is measured for calculation of body mass index; weight will be measured again at 6 and 18-month follow up data collection points. Measuring weight of all consumers at the day program, regardless of their interest in joining the weight loss intervention study, allows for an understanding of: (1) the natural history of weight gain in this population without intervention and (2) how the environmental component of the intervention (i.e., increasing options for healthy meals on-site) may affect weight at the centers in a pre/post fashion. The goal will be to measure height and weight for as many attendees as possible.

For the formal trial, all participants provide written informed consent using procedures reviewed and approved by Johns Hopkins Institutional Review Boards (IRB). A two-stage consent process is used with the first consent obtained to conduct screening procedures and a second consent obtained after baseline data collection and prior to randomization. An evaluation of ability to give consent is also administered for each participant before screening consent which includes answering questions about the goal of the study, what they will be asked to do, and what risks may be involved if they join the study. If a participant is deemed not able to give consent, he/she may not join the study.

Participant eligibility is determined by the completion of several screening measures. The Rose Angina Questionnaire and a checklist of medical conditions are implemented to determine health status for a moderate intensity exercise program [29]. If potential participants have a positive Rose Questionnaire, a prior history of cardiovascular disease or have diabetes mellitus, they require an approval letter from their primary care physician in order to enroll in the study. In addition, primary care physicians for all participants are contacted about the study to ensure there are no contraindications to weight loss or participation in moderate intensity physical activity. Alcohol and substance abuse are assessed with the Addiction Severity Index-Lite [30]; medications are reviewed; and plans to remain at the rehabilitation center during the duration of the study to participate in the trial are discussed with the consumer.

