### Randomization and Blinding

After baseline data collection and before the intervention begins, participants meet with study staff and the intervention arms of the study are described in detail. The study coordinator confirms that the participant meets eligibility criteria, and that all required baseline data have been collected. Participants interested in enrollment are consented individually and randomized to either the intervention or the control group. The study coordinator ascertains and communicates treatment assignments to participants [31]. Randomization is stratified by gender and site using blocks of sizes 2 and 4 in random order to create the randomization sequence for each stratum.

Due to the nature of the intervention, both participants and interventionists will be aware of the assignment. The following mechanisms are in place for data collection staff to be masked to treatment assignment: 1) designating and tracking unmasked study staff; 2) excluding data collection staff from any part of intervention delivery; 3) performing outcome assessments in separate rooms than the intervention; and 4) reminding participants not to share their group assignment. Until the trial end, investigators, staff and participants are masked to outcome data with the exception of the trial statistician and data analyst. In addition, the primary outcome variable, weight, is subject to very little measurement bias [32].

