For the environmental nutrition intervention, the menus are collected at each data collection time point and analyzed for nutrients using ESHA software. The mean number of calories, macronutrients, and micronutrients at each site are determined and t-tests are used to determine significant differences at each time point. Given the expected variability between sites in making changes to menus, differences in menu changes will be assessed within each site and then overall.

To support the long-term goal to integrate the ACHIEVE program into psychiatric rehabilitation centers, a cost analysis is planned. The primary analysis assesses the direct cost per participant of intervention implementation from the perspective of a future payer (e.g., Medicaid). A second analysis assesses costs from the societal perspective projecting cardiovascular risk factor changes 10 years into the future.

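### Both stated menu follow-ups (6 and 18 months) are half a year out of phase with baseline, so a site's before/after menu change cannot be separated from any seasonal menu change

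*Protocol article*

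**What the plan says.** The Environmental Nutrition Intervention section gives three sampling times: "A random sample of menus at baseline, 6 months, and 18 months are collected and evaluated for nutritional content". The consultation goes to each program's kitchen staff, and no site is described as exempt.

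The Data Analysis section describes the timing differently: "the menus are collected at each data collection time point and analyzed for nutrients using ESHA software". On testing it says "t-tests are used to determine significant differences at each time point", and on the level of analysis it says "differences in menu changes will be assessed within each site and then overall". It names no seasonal term.

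Two other places bear on which time points are meant. The Study Design Summary states: "Follow-up data collection occurs at 6, 12, and 18 months from baseline". Under Data Collection and Measurements, the center-wide weighing of all attendees has a shorter schedule: "weight will be measured again at 6 and 18-month follow up data collection points". In Table 1 the row for observing diet at the centers is also marked at baseline, 6 and 18 months only.

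On allocation, the Randomization and Blinding section says "Randomization is stratified by gender and site using blocks of sizes 2 and 4". Individuals are therefore randomized within a site, and both arms share one kitchen.

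**The concern.** Because the kitchens have no concurrent control, the timing of the samples is the only thing in the design that can guard the menu comparison against calendar effects. The stated timing gives no such guard. If a center serves different food in summer and winter, its change from baseline to 6 months mixes that difference with whatever the consultation achieved. The 18-month sample would normally be the check on the 6-month one, but it falls in the same calendar month and carries the same error. Agreement between the two would be reassuring only in appearance.

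The menu data are meant to show whether the environmental component changed the food served. The analysis looks within each site first, and there staggered starts at other sites cannot average season out. Sampling more menus at the same times narrows the interval around a shifted value and does not remove the shift.

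**Working it through.** **Inputs from the article.** Menu times are baseline, 6 and 18 months (Environmental Nutrition Intervention). A 12-month trial visit exists (Study Design Summary; Table 1 marks weight at 12 months). There are 10 sites (Study sites and population). There are no unexposed kitchens. The plan gives no figure for seasonal menu variation, so there is none to reproduce.

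**Step 1: calendar phase.** Take months since baseline modulo 12.

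| Sample | After the intervention began? | Months mod 12 |
|---|---|---|
| Baseline | no | 0 |
| Month 6 | yes | 6 |
| Month 18 | yes | 6 |
| Month 12 (if collected) | yes | 0 |

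With the first three rows alone, the before/after column and the season column are the same variable, so no analysis of a single site can separate them. The fourth row breaks the tie. Month 6 against month 18 is season-matched, but neither sample precedes the intervention.

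**Step 2: spurious change under an annual cycle with no true effect.** Assume the menu mean at calendar time t is mu + A·cos(2πt/12), where A is half the seasonal swing. Let s be the site's start month counted from the seasonal peak. The apparent change at month m is

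A·[cos(2π(s+m)/12) − cos(2πs/12)].

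- At m = 6 and at m = 18 this equals −2A·cos(2πs/12), the same value at both visits.
- At m = 12 it is 0 for every s. This holds for any pattern that repeats yearly, not only a cosine.

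Size at months 6 and 18, by start month:

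- start at a peak or trough: 2A, the full swing
- one month away: 1.73A
- two months away: 1.0A
- three months away (midway): 0
- average size over random starts: 2A × 2/π = 1.27A

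**Step 3: pooled over 10 sites.**

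- Starts spread at random over the year: the mean is about 0. The SD for one site is 2A/√2 = 1.41A, and for the mean of ten it is 1.41A/√10 = 0.45A.
- All starts within a three-month window centered on the peak: −2A × sin(π/4)/(π/4) = −2A × 0.90 = −1.8A.

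**Step 4: illustration in kcal (assumption; the article gives no value).** Let the seasonal swing 2A be 0, 20 or 60 kcal, so A is 0, 10 or 30 kcal.

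| Quantity | A = 0 | A = 10 | A = 30 |
|---|---|---|---|
| One site, start at an extreme (2A) | 0 | 20 | 60 |
| One site, average size (1.27A) | 0 | 13 | 38 |
| One site, start midway | 0 | 0 | 0 |
| Ten sites, random starts, SD (0.45A) | 0 | 4.5 | 13.5 |
| Ten sites, starts clustered at an extreme (1.8A) | 0 | 18 | 54 |
| Any site at month 12 | 0 | 0 | 0 |

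**The case against.** **No evidence of seasonality.** Nothing in the article says that menus vary by season, and site start dates are not given. This stands, and it is why no single figure can be attached to the bias. A reader might infer that every site's change is shifted by the full summer/winter difference. That is true only for a site starting at an extreme; a site starting midway carries none.

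**The two sections may not conflict.** A reader might infer a flat contradiction between the section that lists three times and the one that refers to each data collection point. The article does not support that firmly. The center-wide weighing and the diet-observation row of Table 1 both run at baseline, 6 and 18 months, so the looser wording may mean those same three times. In that case month 12 is simply not sampled. If it does include month 12, the season-matched sample is already intended and the shorter list needs correcting. The wording should be settled under either reading.

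**The chosen times have a rationale.** They match the co-primary weight outcomes, the ends of the intensive and maintenance phases, and the center-wide weights. A reader might conclude that baseline to 12 months should become the main menu contrast. That would detach the menu result from all of these, so the objection stands against promotion. It does not stand against adding a supporting contrast.

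**Month 12 cures only one problem.** An uncontrolled comparison stays exposed to other time trends, such as the financial stress and staff turnover that the Discussion mentions. This is correct, but it is no reason to leave the season question unanswerable.

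**Low consequence.** Menu content is not named in the primary or secondary aims. This is also correct and is reflected in the verdict.

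**Conclusion.** The point holds as a limited design weakness in the menu evaluation. With the stated times, consultation and season are fully aliased within each site, and the second follow-up repeats the error of the first. The aliasing follows from the calendar alone. The size of the resulting bias does not, because it depends on the unknown seasonal swing and the unknown start dates. For one site it lies between zero and the full swing, and averages about 1.27A (64% of the swing) if start months are random and the cycle is a simple annual one. In the pooled result it is centered near zero with SD 0.45A under random starts, but could approach 1.8A if sites start close together at a seasonal extreme.

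A reader might infer that the trial's weight result is affected. It is not: both arms at a site share the same kitchen and are measured concurrently, so seasonal menus do not bias the randomized comparison.

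This is not a detail that a fuller analysis plan could settle alone. Such a plan could adjust for calendar month across staggered sites, but it cannot recover 12-month menus that were never collected. The change is worth making because it is cheap, but nothing primary depends on it.

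**What to change.** Make the Environmental Nutrition Intervention and Data Analysis sections name the same menu times: baseline, 6, 12 and 18 months. Keep baseline to 6 months and baseline to 18 months as the planned contrasts. Add baseline to 12 months as a season-matched supporting contrast, and read the planned contrasts beside it. A change seen at 6 and 18 months but absent at 12 would point to season; a change of similar size at all three would argue against it. Record the calendar month of every menu sample, so that the pooled analysis can show how site starts were spread and, if wanted, adjust for month.

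The cost is one more menu sample per site, about ten in all, to collect and code. Data collectors are already on site for the 12-month weights, and the Intervention Delivery section already lists month 12 for recording staff time. The added contrast will have no center-wide weights beside it, since those are not taken at 12 months, which is a further reason to keep it as support.

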### Data Analysis

Randomly assigned intervention group (i.e., behavioral intervention or control) is the main independent variable for intent-to-treat analysis [47]. The co-primary outcomes are weight loss at 6 and 18 months. To evaluate the efficacy of the intervention for each of these outcomes, generalized estimating equations are used [48]. These models account for the longitudinal nature of the trial and incorporate baseline, and 6, 12 and 18-month measurements and will account for study site and other baseline characteristics found not to be balanced by randomization. For secondary outcomes that are categorical, logistic regression GEE models are used according to the same principles outlined above for continuous outcomes.

In addition to the analyses that preserve the intention to treat principle, analyses on subgroups defined post-randomization are exploratory. These include analyses in participants who attended the majority of weight management and exercise intervention sessions.

Although second generation antipsychotics and other psychotropic medications can induce substantial weight gain [3,9], we expect that both study groups will be equivalent in their distribution of these medication due to the process of randomization. Several analytical approaches are planned to address three main potential effects of antipsychotic and other concomitant medication on study outcomes; these include: (1) imbalances in medication use between the intervention and control groups, despite randomization procedures, (2) variation in intervention efficacy by medication or medication class, and (3) changes in drug use after randomization.

The analytic approach to handle missing data will be anchored on the assumption that data is missing at random (MAR), where the probability of missing can depend on all observed information such as measured weights and covariates but does not depend on variables that are not recorded. The analysis model will include parameters for visit specific means for each treatment group, baseline covariates associated with study retention, and use an unstructured covariance structure. Missing at random is almost never strictly correct, but careful modeling should make the missing data process as close to MAR as possible. Primary analyses will be conducted under the assumption of MAR; sensitivity analyses will be based on sensible "missing not at random" scenarios to evaluate the robustness of the inferences under the MAR assumption.

For the environmental nutrition intervention, the menus are collected at each data collection time point and analyzed for nutrients using ESHA software. The mean number of calories, macronutrients, and micronutrients at each site are determined and t-tests are used to determine significant differences at each time point. Given the expected variability between sites in making changes to menus, differences in menu changes will be assessed within each site and then overall.

To support the long-term goal to integrate the ACHIEVE program into psychiatric rehabilitation centers, a cost analysis is planned. The primary analysis assesses the direct cost per participant of intervention implementation from the perspective of a future payer (e.g., Medicaid). A second analysis assesses costs from the societal perspective projecting cardiovascular risk factor changes 10 years into the future.

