### Sample size and power

The main objective of this trial is to detect weight loss having public health significance. Previous work has indicated that 4-5 pounds of weight loss should reduce systolic blood pressure by ~3 mmHg, which has been estimated to reduce stroke mortality by 6-8%; cardiovascular heart disease mortality by 4-5%; and to reduce risk of incident hypertension by 20% [18,49]. A Monte Carlo simulation study was used to assess the power to detect a clinically meaningful effect on weight loss at months 6 and 18 under a range of conservative assumptions about the effect size, standard deviation, and follow-up with potentially clustered sites [50]. It was assumed that a 4.5 lb difference in weight at 18 months between intervention and control groups would be observed and that the difference at 6 months would be larger. For power calculations, we assumed a standard deviation of change in weight of 12 lbs and that follow-up would be 80% complete. Under these assumptions, for two-sided 0.05-level tests of the null hypothesis, the study should provide approximately 86% power for detecting a difference of 4.5 lbs with SD = 12 lbs. In addition, the study will have the same power to detect the a similar effect size with a smaller sample size if we achieve a higher follow-up rate.

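### The plan names GEE but rests primary inference on MAR, which unweighted GEE does not guarantee: a small to modest exposure for 18-month weight, less protection for categorical secondary outcomes

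*Protocol article*

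**What the plan says.** All of the analysis text is in the protocol article, Data Analysis.

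- **Outcomes and estimator.** "The co-primary outcomes are weight loss at 6 and 18 months". For these, "To evaluate the efficacy of the intervention for each of these outcomes, generalized estimating equations are used [48".
- **Data used.** "These models account for the longitudinal nature of the trial and incorporate baseline, and 6, 12 and 18-month measurements".
- **Categorical secondary outcomes.** For these, "logistic regression GEE models are used according to the same principles outlined above for continuous outcomes".
- **Missing data.** Under the assumption adopted, "the probability of missing can depend on all observed information such as measured weights and covariates". Further on: "Primary analyses will be conducted under the assumption of MAR". Sensitivity analyses under missing-not-at-random scenarios are also planned.
- **Model specification.** The analysis model is to include "parameters for visit specific means for each treatment group, baseline covariates associated with study retention, and use an unstructured covariance structure".

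The section does not say whether the unstructured model is fitted by likelihood or by moment-based estimating equations. It mentions neither weighting nor imputation. Sample size and power assumes "that follow-up would be 80% complete".

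**The concern.** The estimator and the missing-data assumption are stated in the same section and do not match. Ordinary GEE is guaranteed consistent only if missingness does not depend on observed outcomes once covariates are accounted for. The plan allows more than that: a participant's earlier measured weights may drive dropout.

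The arms also differ in ways that could make such dropout arm-specific. Intervention participants have weekly weigh-ins, frequent classes and attendance rewards, whereas controls have quarterly health classes. If people who gain weight leave one arm more readily than the other, the 18-month contrast is the one exposed. Categorical secondary outcomes are exposed too, because they inherit the same approach through a logistic link.

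**Working it through.** **1. The plan's own figure.** Inputs from Sample size and power and Study Design Summary: 320 participants (taken as 160 per arm), 80% follow-up, difference 4.5 lb, SD of change 12 lb, two-sided 0.05.

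- Completers per arm: 160 × 0.80 = 128.
- Standard error: 12 × √(2/128) = 1.5 lb.
- Power: Φ(4.5/1.5 − 1.96) = Φ(1.04) = 85.1% (84.8% by noncentral t).

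The plan states about 86%, so its figure reproduces. The 1.5 lb standard error is a yardstick for the biases below.

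**2. Why unstructured covariance helps, and why it is not a full cure.** GEE solves Σ Dᵢ′Vᵢ⁻¹(yᵢ − μᵢ) = 0 over the observed visits. With a continuous outcome, identity link and visit-by-arm means, these are the same mean equations as the Gaussian likelihood. If V is the true covariance, the 18-month residual enters net of its regression on earlier visits. Under MAR (and linear regressions) that net residual has mean zero. Ordinary GEE, however, estimates V by moments from observed residuals. After selective dropout those come from a selected group, so V is distorted and the cancellation is incomplete. ML or REML estimates V in a way that allows for the missing visits.

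**3. Size for weight at 18 months.** The article does not give the inputs needed, so these are assumptions: baseline SD 45 lb; change SDs 8, 10.5 and 12 lb at 6, 12 and 18 months; correlations of change 0.65 to 0.85; true differences −5.0, −4.5 and −4.5 lb. Dropout after month 6 depends on observed weight change, with log-odds slope per 8 lb as shown. N = 400,000, modelling weights. The cells are the estimated 18-month difference in lb.

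| Slope, intervention / control | Missing at 18 mo, intervention / control | Independence GEE | Exchangeable GEE | Unstructured-correlation GEE | Unstructured-covariance GEE | Unstructured ML |
|---|---|---|---|---|---|---|
| 0 / 0 | 18.9% / 18.9% | −4.36 | −4.53 | −4.53 | −4.53 | −4.53 |
| 1 / 1 | 21.1% / 31.1% | −3.53 | −4.05 | −4.48 | −4.40 | −4.49 |
| 0.5 / 0 | 18.8% / 18.9% | −5.49 | −5.02 | −4.55 | −4.56 | −4.55 |
| 1 / 0 | 21.0% / 19.1% | −6.41 | −5.43 | −4.44 | −4.56 | −4.48 |
| 1 / −1 | 21.1% / 20.5% | −8.44 | −6.39 | −4.53 | −4.86 | −4.50 |

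The structure that the plan states stays within about 0.4 lb of the truth. The largest departure needs opposite dropout in the two arms.

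**4. Weights or change scores.** The outcome is called weight loss, yet the models incorporate baseline, so either scale is possible. Further runs used change SDs of 9, 11 and 12 lb and 20% loss after month 6.

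- Weights, unstructured GEE: off by 0 to 0.34 lb.
- Change scores, dropout related to weight in the intervention arm only, common scale parameter: off by 0.36 lb.
- Change scores, opposite dropout by arm: off by 0.99 lb with a common scale, 0.33 lb with visit-specific variances.

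**5. The 6-month effect.** With dropout only after month 6, every method was unbiased at 6 months. When 7–8% were missing at 6 months depending on baseline weight (N = 150,000), unstructured GEE gave −4.97 to −5.20 lb and ML −4.95 to −4.98 lb, against a true −5.0 lb.

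**6. Stability at the trial's size.** At N = 320, modelling weights, the moment-estimated unstructured matrix was not positive definite in 26% (visit-specific variances) to 75% (common scale) of 400 replicates. It never failed on change scores. This depends on the implementation, but it matters if software or analyst then falls back to a simpler structure.

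**7. Categorical outcomes.** The argument in step 2 does not carry over. With a logistic link the GEE equations are not a likelihood score, so no choice of working correlation secures validity under MAR. No size is given, because the Secondary Aims name no categorical outcome.

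**The case against.** The strongest reply is that the plan already specifies most of the right model. Visit-by-arm means, unstructured covariance, retention covariates and MAR describe a mixed model for repeated measures in all but name. Only the covariance estimation step is open, and a journal article may leave that to the full protocol. Even at 0.4 lb, the bias is 0.4/4.5 = 9% of the target and 0.4/1.5 = 0.27 of a standard error. Sensitivity analyses under missing-not-at-random scenarios are planned as well. The secondary outcomes listed in the Secondary Aims are all naturally continuous.

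Much of this stands, and it sets the severity. It does not remove the point, because the article does not leave the estimator open: it names GEE for weight and logistic GEE for categorical outcomes. Read as written, that means moment-based fitting.

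A reader might infer that the primary analysis is open to biases of 1 lb or more at both 6 and 18 months. The documents do not support that. On weights, biases above 1 lb arise with independence or exchangeable structures, which the plan does not choose, and the 6-month effect is hardly exposed. Nor would a likelihood fit cure everything. If dropout depends on intervention weigh-ins that are not in the model, beyond what the modelled visits capture, it is not protected either.

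**Conclusion.** The mismatch between the named estimator and the stated assumption is real, and its likely effect on the primary result is small to modest. For 18-month weight, under assumed arm-specific, weight-related loss of about 20% after month 6, the bias is roughly 0 to 0.4 lb on weights and up to about 1 lb on change scores. The upper figure is 1/4.5 = 22% of the target difference. It needs a common scale parameter and opposite dropout by arm. Bias is near zero if dropout follows the same pattern in both arms. The standard deviations over time, correlations and dropout slopes are assumptions, and the figures move with them.

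The gap is more fundamental for categorical secondary outcomes, since logistic GEE has no protection from the covariance choice, but its size cannot be stated. Overall severity is moderate to minor. It would be too strong to say that the co-primary analyses are invalid.

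**What to change.** In Data Analysis, replace GEE for weight and the other continuous outcomes with a mixed model for repeated measures fitted by ML or REML. Keep the visit-by-arm means, retention covariates and unstructured covariance already specified. For categorical secondary outcomes, specify multiple imputation followed by the logistic analysis, or inverse-probability-weighted GEE.

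Constraining the baseline means to be equal across arms and using Kenward-Roger degrees of freedom are optional and not needed to cure this point.

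The cost is a change of wording, standard software and slightly more analysis work for the categorical outcomes. No extra data or participants are needed. The downside is reliance on the modelled covariance, which the unstructured form keeps small.
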